# Comparison of high and low intensity contact between secondary and primary care to detect people at ultra-high risk for psychosis: study protocol for a theory-based, cluster randomized controlled trial

**DOI:** 10.1186/1745-6215-14-222

**Published:** 2013-07-17

**Keywords:** Early intervention, Primary care, Psychosis, Cluster randomized controlled trial, Ultra high-risk

## Abstract

**Background:**

The early detection and referral to specialized services of young people at ultra-high risk (UHR) for psychosis may reduce the duration of untreated psychosis and, therefore, improve prognosis. General practitioners (GPs) are usually the healthcare professionals contacted first on the help-seeking pathway of these individuals.

**Methods/Design:**

This is a cluster randomized controlled trial (cRCT) of primary care practices in Cambridgeshire and Peterborough, UK. Practices are randomly allocated into two groups in order to establish which is the most effective and cost-effective way to identify people at UHR for psychosis. One group will receive postal information about the local early intervention in psychosis service, including how to identify young people who may be in the early stages of a psychotic illness. The second group will receive the same information plus an additional, ongoing theory-based educational intervention with dedicated liaison practitioners to train clinical staff at each site. The primary outcome of this trial is count data over a 2-year period: the yield - number of UHR for psychosis referrals to a specialist early intervention in psychosis service - per primary care practice.

**Discussion:**

There is little guidance on the essential components of effective and cost-effective educational interventions in primary mental health care. Furthermore, no study has demonstrated an effect of a theory-based intervention to help GPs identify young people at UHR for psychosis. This study protocol is underpinned by a robust scientific rationale that intends to address these limitations.

**Trial registration:**

Current Controlled Trials ISRCTN70185866

## Background

The detection and prompt referral to early intervention services of young people who may be at ultra-high risk (UHR) for psychosis [1] is intended to reduce the duration of untreated psychosis (DUP) and improve outcomes [2]. Early referral is, therefore, a desirable behavior in professionals who have the opportunity to do so.

General practitioners (GPs; primary care physicians) are usually the healthcare professionals contacted first by individuals at UHR for psychosis [3]. However, early detection of psychosis in primary care is difficult because of the nonspecific nature of behavioral and psychological antecedents of psychosis, and the very low predictive value [4].

Some Scandinavian and Australian projects have developed protocols for the detection of people at UHR for psychosis in professional settings such as primary care [5,6]. However, none of them have evaluated the effectiveness or cost-effectiveness of different approaches. Such analyses may be important because education alone fails to improve the management and identification of mental health problems in primary care [7]. Indeed, a recent educational intervention that attempted to enhance GP skills in the identification of first-episode psychosis (FEP) neither modified referral rates to early intervention services nor reduced the DUP [8].

We present here the design and implementation of the first cluster randomized controlled trial (cRCT) that compares two different approaches to liaising with primary care, in order to increase detection of young people at UHR for psychosis and early referral to a specialist early intervention team. The approach and methodology follows the Medical Research Council (MRC), London, UK, guidelines for the design and evaluation of complex interventions [9].

## Methods/Design

### Cluster randomized controlled trial (cRCT)

#### Aim

To test the null hypothesis that a theory-based educational intervention for primary care, including ongoing personal liaison by specialist health professionals, is not different, in terms of effectiveness and cost-effectiveness, to a postal information campaign coordinated from an office in a specialist, secondary care-based, early intervention service (CAMEO, Cambridgeshire and Peterborough, UK; http://www.cameo.nhs.uk), for detecting individuals aged 16 to 35 years at UHR for psychosis in primary care.

In this cRCT, primary care practices across Cambridgeshire and Peterborough are allocated to one of the following educational groups and referral activity is followed over a period of 2 years:

1.) Low intensity: implementation of the postal information campaign that represents a minimum of good practice.

2.) High intensity: implementation of the postal information campaign plus an additional, ongoing theory-based educational intervention.

#### Identification and recruitment of practices

A total of 104 general practices, working across 138 surgeries (sites), within the geographical boundaries of Cambridgeshire and Peterborough, were identified from the Primary Care Research Network East of England (PCRN EoE; http://www.crncc.nihr.ac.uk/about_us/pcrn/eoe) database. All had practice nurses and varied from single-handed to multi-partner practices, with the largest practice having 15 GPs. They included a mixture of urban, suburban and rural practices.

The original design of the trial was predicated on the presumption that formal consent to take part in the study was not required because the study would not directly involve patients or their care, and was understood in the context of service development within the National Health Service (NHS) in primary care. Clinical equipoise was assumed and resource constraints precluded implementation in all practices. Thus, the trial would involve all practices across Cambridgeshire and Peterborough. However, the Cambridgeshire 1 Research Ethics Committee granted approval on the basis that consent was obtained from general practices to take part in the study, which represented a significant change in the design. Even if formal consent had not been required, the study team would still have needed the agreement of practices in the high intensity arm to undertake elements of the study, such as the educational sessions and distribution of leaflets among staff. The invitation to participate may therefore have influenced referral behavior in practices that did not consent to participate. We are, however, routinely collecting information regarding the number of UHR and FEP referrals from these sites as part of our ongoing clinical service evaluation. We will also analyze the characteristics of these practices in order to evaluate the validity of our findings.

Following the Ethics Committee’s requirements, the partners at each practice were provided with an information sheet (available from the authors) detailing the study. They were then contacted by the PCRN EoE and research team, and asked whether they were interested in taking part. If they expressed interest, a liaison practitioner (LP) visited to obtain a signed consent form from the partner. A GP or nurse at the surgery (site) was identified to act as the point of contact should they be randomized to the high intensity arm.

All the clinical staff from practices randomized to the high intensity arm will be invited to attend educational sessions organized at their respective surgeries, and their time reimbursed by the West Anglia Comprehensive Local Research Network (West Anglia CLRN; http://www.crncc.nihr.ac.uk/about_us/ccrn/west_anglia) as service time spent on the research.

#### Randomization of clusters

General practices were considered as the clusters and randomized at this level, since some practices operated from more than one surgery and shared clinical staff. Practices that consented to participate in the study were stratified according to three high-level factors that were considered, *a priori*, to be likely to relate to referral behavior:

1.) Three levels of geographical area: Cambridge and South Cambridgeshire, Huntingdon and East Cambridgeshire, and Peterborough and Fenland.

2.) GPs working at multiple sites (yes/no).

3.) Membership of the Association of Student Practices in Cambridge (N=8) where university students account for a high proportion (approximately 50%) of the total list size.

Randomized allocation was carried out independently of the research team and occurred after obtaining consent. Randomization was in 12 strata and 96 blocks, with block size 2 (‘ralloc’ command in Stata (StataCorp JP, College Station, TX, USA)) (Figure 1).

**Figure 1 F1:**
[figure not shown]
Flow of practices/surgeries through selection, consent and randomisation processes.

#### Primary outcome

The primary outcome of this cRCT is count data over a 2-year period: the yield - number of UHR for psychosis referrals to a specialist early intervention in psychosis service (CAMEO) - per practice site.

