#### Sample size calculation

We powered the study based on sample size formulae for Poisson outcomes in a completely randomized design. For power of 80% with: 1) a significance level of 0.05 (two-sided); 2) referral counts expressed as an incidence rate of referrals in the low intensity group of 40 per 100,000 person-years [14]; 3) an anticipated incidence rate in the high intensity group of 0.00080 per 100,000 person-years; 4) 2,000 person-years per cluster (the average surgery list size for the age range of 16 to 35 years, per 2 years of study); and 5) a coefficient of variation estimated at a value of 0.15, our calculations required a sample size of 31 surgeries (practice sites) in each arm.

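### Practices are randomised, but the primary outcome, sample size and model work by surgery site with no allowance for sites of one practice; the effect is small at the plan's own variation

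*Protocol article*

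**What the plan says.** All references are to the protocol article.

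- **Randomization of clusters.** The randomised unit and its reason are explicit: "General practices were considered as the clusters and randomized at this level, since some practices operated from more than one surgery and shared clinical staff". Whether GPs work at multiple sites is also a stratification factor.
- **Abstract, Methods/Design.** The primary outcome is the "number of UHR for psychosis referrals to a specialist early intervention in psychosis service - per primary care practice".
- **Primary outcome.** The same outcome becomes the "number of UHR for psychosis referrals to a specialist early intervention in psychosis service (CAMEO) - per practice site".
- **Sample size calculation.** The exposure of 2,000 person-years per cluster is taken from the average surgery list, so a cluster here is a surgery. The conclusion is in the same unit: "our calculations required a sample size of 31 surgeries (practice sites) in each arm".
- **Statistical analysis.** Poisson regression is primary, with zero-inflated or negative binomial models if its assumptions fail. Surgery size enters as the number of GPs at each site. No practice effect, clustered variance or summing over sites is named.
- **Economic analysis.** Here, and only here, the models are said to respect the hierarchy of a cluster trial.
- **Identification and recruitment of practices.** There are 104 practices working from 138 surgeries in the area.

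**The concern.** The primary outcome has two units. The one in the Methods lies below the unit of randomisation. The authors' own reason for randomising practices, shared staff, is a reason to expect that sites of one practice do not refer independently. Those sites also share an arm and, in the high intensity arm, the training.

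An analysis of site rows as independent observations then overstates the information on the treatment effect, and its intervals are too narrow. The fallback models estimate extra variation between site rows, but they still treat two rows of one practice as unrelated. It is also left open which site is credited with a referral by a GP who works at two, and how that GP enters the per-site covariate.

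At stake are the validity of the primary test and the freedom to choose the unit after the counts are known.

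**Working it through.** **Inputs from the Sample size calculation:** power 80%; two-sided 0.05; r0 = 0.0004 per person-year (40 per 100,000); y = 2,000 person-years per surgery; k = 0.15. The high intensity rate is printed as 0.00080 per 100,000 person-years. I read it as r1 = 0.0008 per person-year, because the printed unit gives only about 10 to 11 per arm. That slip is separate from this point.

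**1. The plan's figure.** The usual formula for unmatched clusters with Poisson rates is

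c = 1 + (1.960 + 0.842)² × [(r0 + r1)/y + k²(r0² + r1²)] / (r1 − r0)²

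- (r0 + r1)/y = 0.0012/2,000 = 6.00 × 10⁻⁷
- k²(r0² + r1²) = 0.0225 × 8.0 × 10⁻⁷ = 0.18 × 10⁻⁷
- (r1 − r0)² = 1.6 × 10⁻⁷, so the ratio is 6.18/1.6 = 3.8625
- 7.849 × 3.8625 = 30.3, or 31.3 with the added 1

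The stated 31 is reproduced, with the surgery as cluster. Power at 31 per arm is 79.6% with the added 1 and 80.9% without it.

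**2. The same formula with the practice as cluster.** Assume consenting practices average 138/104 = 1.327 sites and that k = 0.15 applies to practices.

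- y = 2,000 × 1.327 = 2,654 person-years
- (r0 + r1)/y = 4.52 × 10⁻⁷; ratio = (4.52 + 0.18)/1.6 = 2.939
- c = 7.849 × 2.939 = 23.1, or 24.1 with the added 1; rounded up, 24 to 25 practices per arm
- 31 sites correspond to 31/1.327 = 23.4 practices, with power 78.8% (80.5% without the added 1)

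The change of unit costs 0.8 points (79.6 to 78.8) or 0.4 points (80.9 to 80.5).

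**3. Type I error when sites are taken as independent.** Assume 70 one-site and 34 two-site practices (70 + 34 = 104; 70 + 68 = 138), with the practice effect fully shared by its sites. The size-weighted mean is m = (70 × 1 + 34 × 4)/138 = 1.493. With both arms at r0, the true variance relative to the assumed variance is

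D = (r0/y + m·k²r0²) / (r0/y + k²r0²), with y = 2,000, and type I error = 2[1 − Φ(1.96/√D)].

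| k | D | Type I error |
|---|---|---|
| 0.15 | 1.009 | 5.1% |
| 0.5 | 1.082 | 6.0% |
| 1.0 | 1.219 | 7.6% |

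The effect is small because a site expects only 2,000 × 0.0004 = 0.8 referrals in the low intensity arm, so Poisson variation dominates unless k is large.

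**4. Simulation with variance scaling in both models.** Assumed: 48 practices with 62 sites (14 practices with two sites), gamma practice effects, stratified blocks of 2, 40 referrals per 100,000 person-years, and 1,000 to 1,500 trials per setting.

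| k | Site rows | Practice rows |
|---|---|---|
| 0.15 | 4.7% | 4.5% |
| 0.5 | 6.4% | 5.5% |
| 0.8 | 8.3% | 6.6% |

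Each rate has a Monte Carlo standard error of about 0.6 to 0.8 points, so the first row shows no difference and the second barely does. The direction agrees with step 3.

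**The case against.** The best defence is that the article is condensed. A practice random effect or robust variance is commonly left to an analysis plan, and the economic analysis shows that the authors know the data are hierarchical. This stands for the missing term taken alone. It does not settle the conflict: the article itself fixes the outcome, the sample size and the covariate at site level, against its randomisation section and abstract.

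The second defence concerns size. A reader might infer that the stated power is materially wrong. The documents do not support that: 31 reproduces, and the unit costs under 1 point at k = 0.15. At larger k, practice-level power does fall, to 74.3% at k = 0.3 and 64.9% at k = 0.5. But the same formula with independent sites gives 76.2% and 68.8%, so the unit accounts for 1.9 and 3.9 points. Most of the fall comes from replacing the plan's k with values that it does not give.

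A reader might also infer serious inflation of type I error from an unscaled Poisson model on site rows. Under the assumptions of step 3 that model gives 8.5% at k = 0.5, but allowing for overdispersion of site rows already brings it to 6.0%. The plan provides for overdispersion through its fallback models. Only what remains belongs to the choice of unit.

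Finally, the numbers of consenting practices and sites are in a figure that is not shown, and the document does not say how a GP with two sites is counted. Double counting is therefore possible but not established.

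**Conclusion.** The plan is wrong as written on the unit of its primary outcome and analysis, and the size is small. With any positive correlation between sites of one practice, the direction is certain: standard errors too small and type I error above nominal. At the plan's k = 0.15 the effect is negligible. At k of 0.5 to 0.8 it is modest, about 6 to 8% by site against about 5.5 to 6.5% by practice.

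These figures rest on assumed numbers of practices and sites, on a practice effect shared in full by its sites, and on values of k above 0.15 that the document does not give. The case for a change rests on the contradiction and on respecting the randomisation, not on lost power.

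**What to change.** Define the unit once, before the counts are analysed. The simplest choice is the practice: sum referrals, person-years and GPs over its sites, counting each GP once, and fit one row per randomised practice. If site rows are wanted, add a practice random intercept or practice-clustered standard errors with a small-sample correction, and state how referrals and GPs shared between sites are assigned.

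Bring the Abstract, Primary outcome, Sample size calculation and Statistical analysis sections into line with that choice. Restate the requirement in practices: about 24 to 25 per arm at k = 0.15 and 1.33 sites per practice, updated to the sites of the practices that consented.

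The cost is wording, one restated figure and slightly wider intervals. Randomisation and fieldwork need no change.

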#### Secondary outcomes

New trial-initiated referrals will be assessed by the study team and stratified into individuals who meet criteria for UHR for psychosis or FEP according to the Comprehensive Assessment of At-Risk Mental States (CAARMS) questionnaire (true positives) [10], and people who do not fulfill the criteria (false positives).

We will also perform an economic evaluation that will comprise two components:

1.) Evaluation of the short-run cost-effectiveness of both educational strategies in terms of incremental cost per true positive detected.

2.) Evaluation of longer-term cost-effectiveness using decision analytic techniques.

Data on resource use for costing purposes will be recorded using the Adult Service Use Schedule (AD-SUS) modified for early intervention (EI-ADSUS). The EI-ADSUS was designed on the basis of previous economic evidence in relevant mental health populations [11,12] and was adapted for early intervention following consultation with the clinical team and evidence from the literature [13].

#### Sample size calculation

We powered the study based on sample size formulae for Poisson outcomes in a completely randomized design. For power of 80% with: 1) a significance level of 0.05 (two-sided); 2) referral counts expressed as an incidence rate of referrals in the low intensity group of 40 per 100,000 person-years [14]; 3) an anticipated incidence rate in the high intensity group of 0.00080 per 100,000 person-years; 4) 2,000 person-years per cluster (the average surgery list size for the age range of 16 to 35 years, per 2 years of study); and 5) a coefficient of variation estimated at a value of 0.15, our calculations required a sample size of 31 surgeries (practice sites) in each arm.

#### Statistical analysis

In the pre-modeling phase of our analysis, basic descriptive statistics for the total number of referrals, including proportion of true and false positives, will be provided. Subsequent analyses will be carried out separately for true and false positives.

Given that the outcomes are count data, our primary statistical method for modeling will be Poisson regression. If the assumptions of Poisson regression are not met (for example overdispersion), we will use zero-inflated or negative binomial regression models. The fit of the model to the data will be evaluated by comparison of model log-likelihoods. The results will be adjusted for surgery size, considering the number of GPs working in each site as a covariate in the model.

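### If Poisson assumptions fail, the fallback allows a zero-inflated model whose count coefficient need not be the ratio of mean referral yields on which the trial is defined and powered

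*Protocol article*

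**What the plan says.** Under Statistical analysis, the protocol article makes Poisson regression the primary method. If its assumptions are not met, overdispersion being the example given, "we will use zero-inflated or negative binomial regression models". Model fit "will be evaluated by comparison of model log-likelihoods". The results are adjusted for the number of GPs at each site. The text puts neither fallback first and does not say which parameter is the intervention effect if a zero-inflated model is used.

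The Primary outcome section defines the outcome as the two-year count of ultra-high-risk referrals per practice site. The Sample size calculation section compares two overall rates, with "an incidence rate of referrals in the low intensity group of 40 per 100,000 person-years", "2,000 person-years per cluster" and "a coefficient of variation estimated at a value of 0.15". Both sections therefore concern mean yield over all sites, including sites that refer nobody.

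**The concern.** Negative binomial regression changes the variance model but leaves the intervention coefficient as the log ratio of mean counts. Zero-inflated regression does not. It treats the sites as a mixture of some that can only give zero and others that give counts, and its count-part coefficient describes the second group alone. Any effect on the share of never-referring sites goes into the zero part, or is partly lost if that part has no arm term.

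This matters here because the intervention is designed to make GPs begin to identify and refer at-risk patients (Theoretical framework section). An effect on whether a site refers at all is thus a plausible route. If log-likelihood then favours the zero-inflated model and its count coefficient is reported as the result, the trial could report a small or null effect although mean yield had risen as hoped.

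**Working it through.** **1. The plan's own figure.** The inputs come from the Sample size calculation section: λ0 = 0.00040 per person-year, y = 2,000 person-years per cluster, k = 0.15, two-sided α = 0.05 and power 80%. The high-intensity rate is printed as "an anticipated incidence rate in the high intensity group of 0.00080 per 100,000 person-years". I read it as 0.00080 per person-year, because a literal reading gives only about 10 to 11 clusters per arm.

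n = (1.960 + 0.842)² × [(λ0 + λ1)/y + k²(λ0² + λ1²)] / (λ1 − λ0)²

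- (λ0 + λ1)/y = 0.0012/2,000 = 6.00 × 10⁻⁷
- k²(λ0² + λ1²) = 0.0225 × 8.0 × 10⁻⁷ = 0.18 × 10⁻⁷
- n = 7.849 × 6.18 × 10⁻⁷ / 1.6 × 10⁻⁷ = 30.3, rounded up to 31 (31.3 if one cluster is added)

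The stated 31 per arm is reproduced. The design compares expected site means of 0.8 and 1.6, a ratio of 2.

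**2. What the planned inputs imply for the switch.** The variance-to-mean ratio is 1 + k² × mean, which is 1 + 0.0225 × 0.8 = 1.018 and 1 + 0.0225 × 1.6 = 1.036. This is hardly distinguishable from Poisson. Plain Poisson already gives e^−0.8 = 45% and e^−1.6 = 20% of sites with no referral, so many zeros are not in themselves a sign of zero inflation. In simulations with 31 sites per arm and a one-sided 5% likelihood-ratio test as the trigger (an assumption, since the article names none), Poisson was kept in 96% to 97% of trials. A zero-inflated model was used in about 1%.

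**3. A case where the fallback matters.** Illustrative assumption, not in the article: 60% of low-intensity and 20% of high-intensity sites never refer, and the rest have mean 2 in both arms.

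- Site means: 0.4 × 2 = 0.8 and 0.8 × 2 = 1.6, so the ratio of mean yields is 2.
- Ratio among sites that can refer: 2/2 = 1.
- Variance-to-mean ratio, 1 + πμ: 1 + 0.6 × 2 = 2.2 and 1 + 0.2 × 2 = 1.4. Here the overdispersion is marked, so leaving Poisson is likely.

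Simulation of this case, 400 trials with 31 sites per arm:

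| Model | Median ratio for arm | Rejection at 5% |
|---|---|---|
| Poisson, model-based error | 2.03 | 78% |
| Negative binomial | 2.03 | 60% |
| Zero-inflated Poisson, constant zero part | 1.50 | 31% |
| Zero-inflated Poisson, arm in zero part | 1.01 | 4% |

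The 78% is not a fair comparator because its standard error ignores the overdispersion. The like-for-like loss is from 60% to 31% or 4%. Taking the highest log-likelihood picked a zero-inflated model in 77% of trials, or 97% when arm was allowed in the zero part.

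A separate simulation under the same assumption gave a marginal ratio of 1.96 against a count-part ratio of 1.45, and rejection of 54% (Poisson with robust variance) against 27%. It chose the zero-inflated model in 66% of trials even though Poisson was left only after an overdispersion trigger.

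**The case against.** The strongest reply is that the article fixes Poisson as the default and permits a switch only when its assumptions fail. A preset fallback for overdispersed counts is common practice, and comparing log-likelihoods may simply mean a likelihood-ratio test. The threshold, the order of fallbacks and the reported parameter would normally sit in an analysis plan, which is not shown. Most of this stands, and the absence of such detail is not the point made here. What remains is that the article names, as an acceptable replacement for the primary model, one that can estimate something else.

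It is also fair that the shift arises only if a zero-inflated model is chosen and its count coefficient is reported. A marginal mean ratio derived from that model would avoid it. The 60% v 20% split is an assumption too.

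Three stronger readings are tempting and not supported.

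- A reader might infer that the selection inflates type I error. At a coefficient of variation of 0.15, rejection under the null was about 3%. At an assumed 0.5, plain Poisson without selection rejected 7.4% and the model with the highest log-likelihood 6.2%. The excess comes from overdispersion, not from the choice.
- A reader might infer that log-likelihood must favour the larger model. That holds for nested pairs. Negative binomial and zero-inflated Poisson with a constant zero part each add one parameter to Poisson, so their size gives neither an advantage.
- A reader might infer that starting with Poisson contradicts the planned between-cluster variation. That variation adds only 1.8% to 3.6% to the Poisson variance.

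**Conclusion.** The point holds in a conditional form. The outcome and the power calculation rest on mean yield per site, while the stated fallback permits a model whose count coefficient need not be that ratio. At the planned variation the fallback would seldom be reached and little would change. If the effect lies in the share of never-referring sites, overdispersion is marked and the zero-inflated route becomes likely. A true doubling would then be reported as about 1.5 (1.45 to 1.50 in the two simulations), or about 1.0 with arm in the zero part, and power would be halved or worse. These sizes depend on the assumed 60% v 20% split with mean 2 elsewhere, and on the count coefficient being the reported effect. The weakness is in what would be estimated and in power. It is worth correcting before the data are analysed.

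**What to change.** Name one marginal model for the primary result in advance: either negative binomial regression, or Poisson regression with robust or scaled variance. State that the intervention effect is the ratio of mean referral rates between arms.

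Use zero-inflated models only as sensitivity analyses. Express any effect from them as a marginal mean ratio, (1 − π1)μ1 / [(1 − π0)μ0], which in the illustration is 0.8 × 2 / (0.4 × 2) = 2. State that they will not replace the primary result, whatever their log-likelihood.

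The change is to wording only and needs no new data or sites. Its one statistical cost is a slightly wider interval if the counts prove to be pure Poisson.

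### The referral-count model adjusts for size through GP number and names neither the 16–35 person-years nor the stratification factors, which costs precision and power

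*Protocol article*

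**What the plan says.** The outcome is a count: "The primary outcome of this cRCT is count data over a 2-year period", taken per practice site (Primary outcome).

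For the model, the Statistical analysis section states that "our primary statistical method for modeling will be Poisson regression". If its assumptions fail, with overdispersion as the example, "we will use zero-inflated or negative binomial regression models". On adjustment it says: "The results will be adjusted for surgery size, considering the number of GPs working in each site as a covariate in the model".

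Two other sections bear on this:

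- **Sample size calculation.** Power is set on referral rates per person-year, with "2,000 person-years per cluster (the average surgery list size for the age range of 16 to 35 years, per 2 years of study".
- **Randomization of clusters.** Consenting practices were "stratified according to three high-level factors that were considered" in advance to bear on referral: area (three levels), GPs working at multiple sites, and membership of the student-practice association. The last covers eight practices "where university students account for a high proportion (approximately 50%) of the total list size".

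No other section brings person-years or the strata into the referral-count model. The multilevel model under Economic analysis is for costs and cost-effectiveness.

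**The concern.** The trial is planned as a comparison of rates among people aged 16 to 35, but the model's stated measure of size is a headcount of GPs. The two differ wherever the age mix differs, and the protocol itself identifies one such group: practices with about half their list made up of students. Entered linearly under a log link, GP number also makes each extra GP multiply expected referrals by a constant, whereas exposure should act proportionally.

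The strata were chosen because they were expected to predict referral. If they do and are left out of the model, their variation goes into the residual along with the unexplained size variation.

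At stake are the width of the interval for the rate ratio and the chance of detecting the planned doubling. If plain Poisson errors are kept despite the extra scatter, the reported standard error is also too small.

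**Working it through.** **Inputs from the protocol.** Power 80%, two-sided 5%; control rate 40 per 100,000 person-years (0.0004); 2,000 person-years per cluster; between-cluster coefficient of variation k = 0.15; 31 sites per arm. The high-intensity rate is taken as 0.0008 per person-year, the reading that reproduces 31. Its printed unit is a separate matter.

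**Step 1: reproduce 31.** For rates in an unmatched cluster trial:

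c = 1 + (1.96 + 0.84)² × [(r0 + r1)/y + k²(r0² + r1²)] / (r1 − r0)²

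- (r0 + r1)/y = 0.0012/2,000 = 6.0×10⁻⁷
- k²(r0² + r1²) = 0.0225 × 8.0×10⁻⁷ = 1.8×10⁻⁸
- (r1 − r0)² = 1.6×10⁻⁷
- c = 1 + 7.849 × 3.8625 = 31.3 (30.3 without the added 1)

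This agrees with 31. The planned power therefore assumes that sites differ little (k = 0.15) once person-years are accounted for.

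**Step 2: what unexplained variation costs by the same formula.** If unmodelled size and stratum differences raise the effective k:

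| Effective k | Power at 31 per arm | Sites needed per arm |
|---|---|---|
| 0.15 | 80% | 31 |
| 0.25 | 78% | 33 |
| 0.50 | 69% | 40 |
| 0.75 | 57% | 53 |

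**Step 3: the best attainable precision.** Under no effect each arm expects 31 × 2,000 × 0.0004 = 24.8 referrals. Poisson noise alone then gives a standard error of the log rate ratio of √(2/24.8) = 0.284.

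**Step 4: simulate both models.** 62 sites, blocks of 2 within strata, k = 0.15, 3,000 runs per scenario. Referrals were generated in proportion to person-years. Model A has GP number only. Model B has a log person-years offset plus the three factors. Scaled means standard errors inflated for overdispersion, standing in for the negative binomial fallback. The protocol gives none of the scenario values; all are assumed.

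| | Mild | 2 | 3 | Strongest |
|---|---|---|---|---|
| CV of person-years | 0.4 | 0.5 | 0.7 | 0.8 |
| Correlation of GP number with list (log scale) | 0.9 | 0.7 | 0.5 | 0.3 |
| Area step in log rate | 0 | 0.3 | 0.5 | 0.7 |
| Student-site list multiplier | 2.5 | 2.5 | 3 | 4 |
| SD of log rate ratio under no effect, A / B | 0.309 / 0.297 | 0.322 / 0.305 | 0.368 / 0.317 | 0.385 / 0.319 |
| Median plain Poisson SE, A | 0.292 | 0.297 | 0.302 | 0.310 |
| Type I error, plain, A / B | 5.8% / 4.6% | 6.2% / 4.8% | 9.6% / 4.4% | 10.1% / 4.1% |
| Type I error, scaled, A / B | 4.2% / 3.9% | 4.1% / 4.1% | 5.0% / 3.9% | 3.8% / 3.5% |
| Power at rate ratio 2, scaled, A / B | 72.2% / 77.4% | 68.4% / 77.0% | 59.8% / 74.9% | 47.2% / 71.5% |

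The variance ratio A to B under no effect runs from (0.309/0.297)² = 1.08 to (0.385/0.319)² = 1.46. Simulation error on a 5% rejection rate is √(0.05 × 0.95/3,000) = 0.4 points, so the 5.8% is only about two such errors above nominal.

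**Step 5: which part matters.** Further simulations of 62 sites with k = 0.15, all compared on scaled power at rate ratio 2:

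- Referrals proportional to GP number, no student effect: 78.5% with the GP covariate, 78.8% with the offset. The linear shape alone costs almost nothing.
- The same, with 5 of 62 sites assumed to have twice the 16–35 share: 74.4% against 80.0%.
- GP number imperfectly correlated with list size, student sites with twice the list, no stratum rate effects: 70% against 77%.
- The same, with assumed area rate ratios 0.6/1/1.6 and student ratio 0.6: 68% with GP number, 69% with the offset, 76% with the offset plus strata. With weak strata the gain from adding them was negligible.

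**The case against.** Four arguments favour the plan, and each stands in part.

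1. **The text does not say that GP number is the sole adjustment.** A reader might infer that the strata are excluded. The article fixes how size is handled; it is a condensed account, and a full covariate list could sit in an analysis plan that is not shown. So the choice of GP number is the firm part of this point, and the absence of the strata is the softer part.
2. **The fallback deals with overdispersion.** A reader might infer that the planned analysis has the wrong error rate. That holds for plain Poisson only. With errors scaled for overdispersion the GP-only model kept type I error at 3.8–5.0%. What the fallback cannot do is recover lost precision.
3. **The outcome is defined as a count and the intervention targets GPs,** so adjusting for GP number is coherent. The main simulations also generate referrals in proportion to person-years, which makes the offset right by construction. Both remarks are fair. But the sample size is stated in person-years, so the offset matches the effect the trial was powered to detect.
4. **The sizes rest on unknowns.** The protocol gives neither the distribution of GPs per site nor the number of student practices enrolled; the 15 GPs it mentions are for the largest practice, not the largest site. This stands, and is why a range is shown.

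**Conclusion.** The point holds as a recommendation about precision. The stated size adjustment is not the exposure on which the trial was powered, and the text does not carry the randomisation factors into the model.

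Under the assumed scenarios, with overdispersion-scaled errors, the power loss at a rate ratio of 2 is about 5 points in the mild case and about 24 in the strongest. It is near zero if referrals follow GP number with no student effect. Under plain Poisson the standard error is somewhat too small, with type I error of about 6–10%. These figures depend on assumed list-size variation, stratum effects and numbers of student sites, and they treat sites as independently randomised although practices were the unit.

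A reader might also infer a biased treatment effect. The documents do not support that: allocation was randomised within strata, so what is affected is precision and the standard error, not the expected value of the estimate.

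**What to change.** In the Statistical analysis section, or in the analysis plan before the data are analysed:

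- Use log(registered list aged 16–35 × years of follow-up) per site as an offset, so that the reported effect is the planned rate ratio.
- Add area (three levels), multi-site working (yes/no) and student practice (yes/no) as main effects. Main effects are preferable to all 3 × 2 × 2 = 12 cells, some of which will be sparse.
- Keep GP number as an optional extra covariate.
- Keep the overdispersion fallback, with the same offset and factors.

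The cost is an age-specific list size for each site (the sample size already used an average) and 2 + 1 + 1 = 4 degrees of freedom. Sample size and trial conduct do not change.
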